### Eligibility

Detailed inclusion and exclusion criteria are specified in Table 1.

**Table 1 Tab1:** Subject inclusion and exclusion criteria

Inclusion criteria	Exclusion criteria
• GD and GO onset ≤ 12 months • No previous GD treatment other than ATD • First relapse after decrease of antithyroid medication within 4–6 months • GO treatment with glucocorticoids based on the Kahaly scheme • Patients under ATD with normal thyroid function or subclinical hyperthyroid function and moderate-to-severe GO • Clinically active inflammation according to CAScore (≥ 3/7) • Informed consent	• GD and GO onset ≥ 12 months • More than one relapse of GO longer than 6 months from diagnosis • Previous GD treatment by RAI or surgery • SNI greater than 7.0 • Urgent orbital decompression surgery • Loss of vision • Loss of visual field • Loss of color vision • Patients not receiving glucocorticoids for GO • Cytological findings of postsurgical histopathological results suspicious for malignancy • Pregnancy or breastfeeding • Contraindication to GC • Halt of GC therapy • Patients with diabetes mellitus • Age below 18 years • No informed consent

Legend: *ATD* antithyroid drugs, *CAScore* Clinical Activity Score, *GC* glucocorticoid, *GD* Graves' disease, *GO* Graves' ophthalmopathy, *RAI* radioiodine ablation

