### Interventions

#### Pre-treatment interventions

At this screening visit, baseline data in the form of a case report will be documented, including past medical history, current medications, blood parameters, eye examination including slit-lamp bimicroscopy, indirect fundoscopy, visual acuity determination, Hertel exophthalmometry, ocular motility, CAScore and NOSPECS score as well as ocular ultrasound and quality of life questionnaire in German (see Additional file 1). Patients will then be randomized into one of the two treatment groups. All trial data will be collected and documented in the case report form (CRF) (see Additional file 2).

Tables 2 and 3 describe the muscle index (MI) and superonasal index (SNI).

**Table 2 Tab2:** Muscle index (MI)

Normal MI:	< 5.0	
Mild Graves’ orbitopathy	4.5–5.5	Grade I
Moderate Graves’ orbitopathy	5.5–6.5	Grade II
Severe Graves’ orbitopathy	> 6.5	Grade III

**Table 3 Tab3:** Superonasal index (SNI)

Normal SNI	< 5.75	
Danger for optic nerve compression	> 7.0	Grade IV

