#### Surgical intervention: thyroidectomy

The responsible surgeon will document the surgical intervention and any particulars that may have occurred during or following surgery. A standardized surgical approach to the thyroid will be conducted in that a total thyroidectomy will take place.

On the first post-operative day, blood analyses of calcium and parathyroid hormone will be performed. One the second post-operative day the patient will undergo a postoperative ear-nose-throat examination to determine the functionality of the recurrent laryngeal nerve on both sides following the operation.

All patients will receive intravenously administered glucocorticoids (250 mg methylprednisolone) according to our therapy scheme following surgery once a week for 4 weeks.

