#### Drug intervention: ATD

Patients randomized into the ATD group will continue to receive ATD in standard dosages for their hyperthyroidism and GO. They will continue to come for follow-up roughly every 8 weeks.

These patients will also undergo a 4-week intravenous therapy with 250 mg methylprednisolone once a week.

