### Statistical analysis

The data will be analyzed according to the intention-to-treat principle. This means, that for patients with missing MI values at follow-up measurements a conservative value will be imputed. If patients have a SNI >  7 during follow-up, which requires additional treatment, later MI values will be estimated using last value carried forward. The primary and continuous secondary endpoints will be analyzed using repeated measures analysis of covariance, using the randomization group as factor and the baseline values of MI as covariate. The contrast of main interest is the difference between groups in the means computed over all post-randomization measurements. MI and SNI will be obtained before randomization and 1 year after the conducted therapy. Quality of life questionnaire will also be obtained before randomization and after 1 year of follow-up. Further binary secondary endpoints will be analyzed by Mantel-Haenszel tests stratified for the clinical MI grading at baseline. All secondary endpoints will be analyzed at the specified time points (see Tables 4 and 5) and reported and thus no correction for multiple testing is done. Any analyses that will be conducted, but which are not mentioned in the study protocol, will be interpreted as explorative. A statistical analysis plan detailing all statistical computations will be completed prior to the lock of the database. Values are given as *p* values and odds ratio (95% confidence interval); *p* values < 0.05 are considered statistically significant. Analysis of data will be performed using SPSS (Statistical Package for Social Sciences, Chicago, IL, USA) v21 for Windows.

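### Table 1 excludes on post-surgical histology, a finding that in practice arises only after randomisation and only in operated patients; applied as written, it conflicts with the intention-to-treat analysis

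*Protocol article*

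**What the plan says.** **Eligibility, Table 1.** The exclusion column contains "Cytological findings of postsurgical histopathological results suspicious for malignancy". It also contains "Previous GD treatment by RAI or surgery", and the inclusion column requires "No previous GD treatment other than ATD".

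**Pre-treatment interventions.** After screening and baseline documentation, "Patients will then be randomized into one of the two treatment groups".

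**The two arms.** In the surgical arm "a total thyroidectomy will take place". In the comparator arm, "Patients randomized into the ATD group will continue to receive ATD in standard dosages for their hyperthyroidism and GO".

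**Statistical analysis.** "The data will be analyzed according to the intention-to-treat principle". The section explains this by imputing a conservative value for missing MI. It gives no rule for a randomised patient who meets an exclusion criterion once the specimen has been examined. Under Safety aspects, the principal investigator may withdraw a patient at any time. Nowhere does the article say that a patient with suspicious histology stays in follow-up or in the analysis.

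**The concern.** An exclusion criterion should rest on information that exists before allocation and is available in the same way in both arms. Histology of the removed thyroid meets neither condition. It comes from the trial operation, and an antithyroid drug (ATD) patient with the same undetected lesion has no specimen and remains in the trial.

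If the criterion is used, membership of the thyroidectomy arm depends on a finding made after treatment, while membership of the ATD arm does not. The groups compared are then no longer those formed by randomisation. Adjusting for baseline MI does not restore comparability, because the selection rests on something observed later and in one arm only. Randomisation carries extra weight here, since only the assessing ophthalmologist is masked.

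**Working it through.** **1. When, and in whom, can the criterion be met?**

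- Before randomisation: Table 1 admits only patients treated with ATD and bars earlier surgery for GD. No eligible patient should bring post-surgical thyroid histology from GD treatment.
- After randomisation, thyroidectomy arm: every patient treated as allocated yields a specimen.
- After randomisation, ATD arm: no operation is planned, so there is no specimen. A later operation could produce one, but that too follows allocation.

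The histology part thus has no pre-randomisation use in practice, and under allocated treatment it can apply to one arm only.

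**2. The plan's own sample size.** Inputs from Power calculation: difference 0.7, SD 0.8, two-sided level 0.05, two-group t test, 29 per group. Noncentrality = 0.7 / (0.8 × √(1/n1 + 1/n2)). For 29 v 29 this is 3.33, and the noncentral t gives 90.6% power; 28 v 28 gives 89.5%. The stated 29 per group at 90% reproduces.

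**3. Power if patients are lost from the thyroidectomy arm only.** Sixty patients in equal groups means 30 per arm.

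| Thyroidectomy v ATD | Patients lost | Power |
|---|---|---|
| 30 v 30 | 0 | 91.5% |
| 29 v 30 | 1 | 91.0% |
| 28 v 30 | 2 | 90.5% |
| 27 v 30 | 3 | 90.0% |

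**4. How often might it happen?** The documents give no rate. Assume 3-10%: 0.03 × 30 = 0.9 and 0.10 × 30 = 3, so about 1 to 3 patients. The chance of at least one is 1 − (1 − rate)^30: 1 − 0.97^30 = 60% and 1 − 0.90^30 = 96%.

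**5. Shift in the arm mean.** If k of 30 patients are removed and their mean MI change differs by D from that of the rest, the arm mean moves by (k/30) × D. D is also an assumption, taken as 0.5 to 1.0.

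- k = 1, D = 0.5: (1/30) × 0.5 = 0.017, or 2% of 0.7.
- k = 3, D = 1.0: (3/30) × 1.0 = 0.10, or 14% of 0.7.

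For scale, the standard error of the difference at 30 v 30 is 0.8 × √(2/30) = 0.21, so the upper figure is about half a standard error. If D = 0, the expected shift is zero. A harsher assumption of 20% removed (k = 6) with D = 0.8 gives 0.20 × 0.8 = 0.16, or 23% of 0.7, with power 88.0% at 24 v 30.

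**The case against.** **Removal is inferred.** A reader might infer that the plan removes randomised patients and that intention-to-treat is already broken. The documents do not go that far. The criterion stands in an eligibility table, not in a withdrawal rule or a definition of the analysis set, and the only statement on the analysis population is intention-to-treat. One could follow that statement and keep everyone. This stands, and it makes the point conditional. It does not dispose of it: a criterion that cannot operate before randomisation has no use unless it is applied afterwards, and no text says that it is not.

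**The wording is garbled.** If the word of is a slip for or, the cytology part is a legitimate baseline criterion in both arms. This also stands. The post-surgical part remains confined to operated patients on either reading. Histology from an earlier thyroid operation for another reason is conceivable, since Table 1 bars only GD surgery, but that is a strained reading.

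**Imputation would cover it.** Imputing MI for such patients would keep them in the count, but it would replace outcomes that could have been measured with assumed values, in one arm only.

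**Glucocorticoid halt.** A reader might also infer the same contradiction from "Halt of GC therapy", because both arms receive a further glucocorticoid course after allocation. The documents do not support this. The entry reads naturally as a halt during the 12-week course given before randomisation, and it is not specific to one arm. Statistical analysis also keeps patients who develop a superonasal index above 7, another listed exclusion, in the analysis by carrying the last value forward. Listed exclusions are therefore not generally treated as reasons for removal after randomisation.

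**The effect is small.** Agreed. No mechanism in the documents links suspicious histology to MI change, and both quantities behind the shift are assumed.

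**Conclusion.** The criterion is wrong as written. Its post-surgical histology part can in practice be met only after randomisation and only by operated patients. If it is applied, it conflicts with the intention-to-treat statement. On assumed rates of 3-10% and an assumed D of 0.5-1.0, the shift is about 0.02-0.10 MI units, in an unknown direction, with negligible loss of power.

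This does not show that the primary result would be materially biased, nor that anyone has been or will be removed. It is a modest and avoidable selection bias that should be corrected. It is not a defect that by itself threatens the trial.

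**What to change.** 1. In Table 1, delete the reference to post-surgical histopathology. If a malignancy criterion is wanted, limit it to findings available before randomisation in both arms, for example cytology.
2. Under Statistical analysis, add one sentence: randomised patients with suspicious post-surgical histology stay in follow-up, including the 1-year ultrasound, and in the intention-to-treat analysis. An analysis without them is a sensitivity analysis only.

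The cost is a one-line amendment to Table 1 and one added sentence, with no extra patients. The change concerns who is followed and analysed, not how such patients are treated clinically. It should be in place before anyone leaves follow-up on this ground, because a 1-year MI that was not measured cannot be recovered.

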### Consent

Before being admitted to the clinical study, the patient will have a pre-treatment visit to give informed consent. During this visit, the patient will be screened and informed about the study procedures, risks, benefits and data management.

### Procedures for blinding and minimizing bias

Several methods are used in order to minimize random and systematic sources of bias. To minimize selection bias, our inclusion and exclusion criteria are precisely defined. Screening lists and case report files are monitored by independent monitors from the Clinical Trials Coordination Center to ensure correct patient recruitment and meticulous documentation. In order to achieve equal groups of patients free from systematic selection bias, an Internet-based computer randomization is performed after informed consent.

The Internet-based computer randomization is executed using the Randomizer for Clinical Trials (version 1.8.1, Institute for Medical Informatics, Statistics and Documentation, Medical University of Graz, Graz, Austria). The randomization is carried out to generate equal treatment groups by minimizing selection bias. Stratification reduces bias. The trial will only be performed at the Vienna General Hospital in high-volume departments minimizing bias due to learning effects. No additional surgical training has to be done as a standard thyroidectomy will be performed. No additional ophthalmology training has to be done, as the patients will be seen by physicians specialized in the field of GO.

The study will be conducted as a prospective, randomized clinical trial with observer-masked analysis. Every patient receiving follow-up will wear a scarf on their neck to mask any thyroidectomy scars, should there be one present. The ophthalmologist who conducts the follow-up measurements will not be allowed to look into the patient’s file to see which treatment they received. Thereafter, a second non-masked ophthalmologist will resume medical evaluation, treatment and further patient guidance beyond the study protocol.

### Interventions

#### Pre-treatment interventions

At this screening visit, baseline data in the form of a case report will be documented, including past medical history, current medications, blood parameters, eye examination including slit-lamp bimicroscopy, indirect fundoscopy, visual acuity determination, Hertel exophthalmometry, ocular motility, CAScore and NOSPECS score as well as ocular ultrasound and quality of life questionnaire in German (see Additional file 1). Patients will then be randomized into one of the two treatment groups. All trial data will be collected and documented in the case report form (CRF) (see Additional file 2).

Tables 2 and 3 describe the muscle index (MI) and superonasal index (SNI).

**Table 2 Tab2:** Muscle index (MI)

Normal MI:	< 5.0	
Mild Graves’ orbitopathy	4.5–5.5	Grade I
Moderate Graves’ orbitopathy	5.5–6.5	Grade II
Severe Graves’ orbitopathy	> 6.5	Grade III

**Table 3 Tab3:** Superonasal index (SNI)

Normal SNI	< 5.75	
Danger for optic nerve compression	> 7.0	Grade IV

#### Kahaly scheme

All patients will initially receive glucocorticoids for 12 weeks according to the Kahaly scheme [34]. Dosage: 500 mg methylprednisolone given intravenously once a week for 6 weeks followed by a reduction to 250 mg methylprednisolone intravenously once a week for 6 weeks.

All patients will also initially receive ATD. They will come every 4–8 weeks for follow-up. Patients suffering a relapse after 4–6 months will be randomized.

#### Surgical intervention: thyroidectomy

The responsible surgeon will document the surgical intervention and any particulars that may have occurred during or following surgery. A standardized surgical approach to the thyroid will be conducted in that a total thyroidectomy will take place.

On the first post-operative day, blood analyses of calcium and parathyroid hormone will be performed. One the second post-operative day the patient will undergo a postoperative ear-nose-throat examination to determine the functionality of the recurrent laryngeal nerve on both sides following the operation.

All patients will receive intravenously administered glucocorticoids (250 mg methylprednisolone) according to our therapy scheme following surgery once a week for 4 weeks.

#### Drug intervention: ATD

Patients randomized into the ATD group will continue to receive ATD in standard dosages for their hyperthyroidism and GO. They will continue to come for follow-up roughly every 8 weeks.

These patients will also undergo a 4-week intravenous therapy with 250 mg methylprednisolone once a week.

#### Post-treatment interventions

If at any point there is an aggregation of the GO, a third glucocorticoid cycle can be administered.

After both interventions, all patients will be seen in four follow-up appointments where the same parameters will be examined, as mentioned above in the pre-treatment intervention. At the first follow-up 8 weeks following treatment, a blood test will be conducted and a CRF with the blood parameters and current medications will be filled out. The second follow-up 16 weeks following treatment will include a case report with current medications, blood parameters, eye examination including slit-lamp bimicroscopy, indirect fundoscopy, visual acuity determination, Hertel exophthalmometry, ocular motility, CAScore and NOSPECS score and ocular ultrasound. The third follow-up 32 weeks following treatment contains the same case report and parameters as the second follow-up. The last follow-up 1 year after treatment will again include a case report with current medications, blood parameters, eye examination including slit-lamp bimicroscopy, indirect fundoscopy, visual acuity determination, Hertel exophthalmometry, ocular motility, CAScore and NOSPECS score and ocular ultrasound as well as the final quality of life questionnaire. Figure 1 is a flow-chart of the interventions. Figure 2 illustrates the study schedule. Tables 4 and 5 list pre-treatment and post-treatment parameters to be examined.

**Fig. 1 Fig1:**
[figure not shown]
Flow-chart of the interventions

**Fig. 2 Fig2:**
[figure not shown]
Study schedule

**Table 4 Tab4:** Pre-treatment schedule and parameters examined

	Initial screening until randomization						
	Day 1 (initial screening)	Day 2 (4–8 weeks after day 1)	Day 3 (4–8 weeks after day 2)	Day 4 (4–8 weeks after ATD reduction)	Day 5 (12–16 weeks after ATD reduction)	Day 6 (20–24 weeks after ATD reduction	
Pregnancy test	X	X	X	X	X	X	Randomization and treatment
Blood tests	X	X	X	X	X	X	
Slit-lamp bimicroscopy	X					X	
Indirect fundoscopy	X					X	
Visual acuity determination with Snellen test	X					X	
Hertel exophthalmometry	X					X	
Ocular motility, cover test, prism cover test, convergence	X					X	
CAScore/NOSPECS	X					X	
Ultrasound						X	
Adverse events		X	X	X	X	X	
Quality of life form	X						
Case report form	X	X	X	X	X	X	
Blood parameter form	X	X	X	X	X	X	
Current medication form	X	X	X	X	X	X	
Eye examination form	X					X	

Legend: *ATD* antithyroid drugs, *CAScore* Clinical Activity Score, *NOSPECS* No signs/symptoms, Only signs/no symptoms, Soft tissue involvement, Proptosis, Extraocular muscle involvement, Corneal involvement, Sight loss

**Table 5 Tab5:** Follow-up schedule and parameters examined

Follow-up schedule				
	Follow-up 1 (8 weeks following treatment)	Follow-up 2 (16 weeks following treatment)	Follow-up 3 (32 weeks following treatment)	Follow-up 4 (1 year following treatment)
Pregnancy test	X	X	X	X
Blood test	X	X	X	X
Slit-lamp bimicroscopy		X	X	X
Indirect fundoscopy		X	X	X
Visual acuity determination with Snellen test		X	X	X
Hertel exophthalmometry		X	X	X
Ocular motility, cover test, prism cover test, convergence		X	X	X
CAScore/NOSPECS		X	X	X
Ultrasound				X
Adverse events	X	X	X	X
Quality of life form				X
Case report form	X	X	X	X
Blood parameter form	X	X	X	X
Current medication form	X	X	X	X
Eye examination form		X	X	X

### Safety aspects

All adverse events (AE) and serious adverse events (SAE) have to be reported to the principal investigator and the local Ethics Committee, as well as the Clinical Trials Coordination Center. Patients may be withdrawn from the study at any time either at their own request or at the request of the principal investigator. All AE and SAE of both treatment groups will be demonstrated in comparison considering severity and causality in a safety analysis. Safety interim analyses are planned each year and the independent Data and Safety Board will follow the progress of the trial to control the safety. Data management will be done according to International Council for Harmonization-Good Clinical Practice (ICH-GCP). All data will be collected by the study coordinator ([name]). All data will be pseudonymously and securely stored in order to maintain confidentiality by the study coordinator.

### Power calculation

The main study outcome variable will be muscle index (MI), where a difference of 1 corresponds to a difference of one clinical grade (grade II or grade III). We assume, that a proportion of patients (in both treatment groups) will not respond to their treatments. Therefore, an observed difference in MI of 0.7 is defined as clinically relevant in the study. A sample size of 29 in each group will have 90% power to detect a difference in mean changes of 0.7, making a conservative assumption about the standard deviation of the changes of 0.8, and using a two-group *t* test with a two-sided significance level of 0.05 (nQuery Advisor 7.0). At randomization patients will be stratified according to their MI grading (grade II versus grade III).

### Statistical analysis

The data will be analyzed according to the intention-to-treat principle. This means, that for patients with missing MI values at follow-up measurements a conservative value will be imputed. If patients have a SNI >  7 during follow-up, which requires additional treatment, later MI values will be estimated using last value carried forward. The primary and continuous secondary endpoints will be analyzed using repeated measures analysis of covariance, using the randomization group as factor and the baseline values of MI as covariate. The contrast of main interest is the difference between groups in the means computed over all post-randomization measurements. MI and SNI will be obtained before randomization and 1 year after the conducted therapy. Quality of life questionnaire will also be obtained before randomization and after 1 year of follow-up. Further binary secondary endpoints will be analyzed by Mantel-Haenszel tests stratified for the clinical MI grading at baseline. All secondary endpoints will be analyzed at the specified time points (see Tables 4 and 5) and reported and thus no correction for multiple testing is done. Any analyses that will be conducted, but which are not mentioned in the study protocol, will be interpreted as explorative. A statistical analysis plan detailing all statistical computations will be completed prior to the lock of the database. Values are given as *p* values and odds ratio (95% confidence interval); *p* values < 0.05 are considered statistically significant. Analysis of data will be performed using SPSS (Statistical Package for Social Sciences, Chicago, IL, USA) v21 for Windows.

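### Carry-forward after treated SNI > 7 and a single fill-in for missing MI replace primary-outcome data, despite the intention-to-treat claim, and the value carried is not identified

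*Protocol article*

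**What the plan says.** All references are to the protocol article.

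- **Primary variable.** Power calculation: "The main study outcome variable will be muscle index (MI), where a difference of 1 corresponds to a difference of one clinical grade". The same section says "an observed difference in MI of 0.7 is defined as clinically relevant in the study".
- **Missing MI.** Statistical analysis, directly after the intention-to-treat claim: "for patients with missing MI values at follow-up measurements a conservative value will be imputed". The value is not defined in the article.
- **MI after SNI > 7.** Same section: if SNI exceeds 7 during follow-up and additional treatment is needed, "later MI values will be estimated using last value carried forward".
- **Other additional treatment.** Post-treatment interventions: if GO gets worse, "a third glucocorticoid cycle can be administered". No MI rule is attached to this.
- **Schedule of MI and SNI.** Objective of the study and Statistical analysis place both before randomization and at 1 year. In Table 5 the only follow-up ultrasound is under "Follow-up 4 (1 year following treatment"). Post-treatment interventions, however, lists ocular ultrasound at week 16 and repeats the same parameters at week 32.
- **Contrast.** Statistical analysis: the group difference in means over all post-randomization measurements, from a repeated measures analysis of covariance.
- **Entry and threshold.** Table 1 excludes SNI above 7.0. Table 3 labels that range as a danger to the optic nerve.

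**The concern.** Carry-forward here is not a way of handling missing data. The patient is still in follow-up and a 1-year scan is due, but the analysis uses an older number in its place. That conflicts with the intention-to-treat claim in the same paragraph, and it does so under every reading of the schedule.

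What the older number means is left open. Because SNI above 7.0 is an exclusion, a patient who passes 7 in follow-up has worsened. Carrying the baseline records that patient as unchanged. Carrying the MI from the scan that found the high SNI records the worsening and then holds it fixed, whatever happens afterwards. The same patient can thus contribute two quite different values, depending on a choice the article does not state.

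Two kinds of additional treatment are also handled differently. MI after treatment for SNI > 7 is replaced; MI after a third glucocorticoid cycle is not.

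For missing MI, one fixed value is analysed as though it had been measured. No single value is conservative for a comparison of two arms if the arms lose different numbers of patients: it penalises or favours whichever arm has more gaps. The estimate and nominal 5% error rate of the primary comparison are at stake.

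**Working it through.** **1. The plan's own figure.** Inputs from Power calculation: difference 0.7, SD of change 0.8, two-sided 0.05, t test, 29 per group. The noncentral t distribution with noncentrality 0.7 / (0.8 × √(2/n)) gives 89.5% power at n = 28, 90.6% at n = 29 and 91.5% at n = 30 (60 patients in all). The stated 29 for 90% reproduces; the sample size is not in error.

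**2. Which MI can be carried.**

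| Reading of the schedule | MI available when SNI > 7 is found before 1 year | Effect of the rule |
|---|---|---|
| Baseline and 1 year only; MI from the detecting scan not counted | Baseline | Change set to 0 |
| Baseline and 1 year only; MI from the detecting (unscheduled) scan counted | MI at detection | Frozen before additional treatment |
| Scans also at weeks 16 and 32 | Usually a post-baseline MI | Frozen at or before detection |

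Under the first two rows, an SNI > 7 first seen at the 1-year scan has no later MI to replace, so the rule can act only after an unscheduled scan.

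**3. Size of the carry-forward shift.** Let p be the share of an arm affected, C the carried change and A the actual 1-year change. The arm mean moves by p × (C − A).

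- *Baseline carried*, true worsening D: C = 0 and A = D, so the ATD minus Tx difference moves by −(p_ATD − p_Tx) × D.
 - 10% v 0%, D = 1.0: 0.70 − 0.10 = 0.60. With SD held at 0.8 and 30 per arm, power is 81.5% instead of 91.5%.
 - 5% v 15%, D = 1.0: 0.70 + 0.10 = 0.80.
 - Equal shares: no shift.
- *Detection MI carried*, and MI then falls by R after additional treatment: C − A = R, so the arm mean moves by +p × R. With 10% v 0% and an assumed R = 1.0: 0.70 + 0.10 = 0.80. For the same event shares, the two readings push in opposite directions.

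The power figure for 0.60 is the softer part. If ATD changes by −0.3 on average and the worsening patients are allowed to widen the spread, power goes from about 88% to about 83%. The shift in the estimate does not depend on this.

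**4. Single value for missing MI.** If the value filled in differs from the arm's true mean change by G, the arm mean moves by (missing share) × G.

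- Suppose the value were no change, both arms truly improved by 1.0 and missingness were 5% v 20%. The spurious difference is (0.20 − 0.05) × 1.0 = 0.15. Simulation (30 per arm, SD 0.8, 40,000 trials) gives a type I error of about 11%.
- The same with both arms improving by 0.5: 0.15 × 0.5 = 0.075, type I error about 7%.
- Equal 10% missingness, changes of −0.3 and −1.0: 0.9 × 0.7 = 0.63, power about 86%. With equal missingness and no true effect, the error rate stays near 5%.

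**5. Standard error.** With 10% missing per arm and a fill-in near the arm mean, the analysed SD shrinks to 0.8 × √0.9 = 0.759 and the standard error to 0.759 × √(2/30) = 0.196. The 27 patients per arm actually observed support 0.8 × √(2/27) = 0.218. A fill-in far from the mean widens the spread instead, but the imputed values are still counted as measured.

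All event shares, worsening, improvement and missingness rates in steps 3 to 5 are assumptions; the article gives none.

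**The case against.** A reader might infer that the rule scores every deteriorating patient as unchanged. The article does not support that. SNI and MI are both ultrasound measures, so a scan showing SNI > 7 would normally give an MI too, and only later values are replaced. On that reading the patient counts as worsened. The text listing scans at weeks 16 and 32, and the contrast over all post-randomization measurements, also fit a plan with several MI values. This stands: scoring as unchanged is one possible result, and it concerns carry-forward only, not the conservative value.

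A reader might also take 11% as the trial's type I error. It is not. No change as the fill-in is a supposition; the article does not define the value, and a SAP not shown may do so. What does not depend on that definition is that the article commits to one imputed value per gap.

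Freezing MI before additional treatment can also be defended as keeping the effect of that treatment out of the comparison. That is a legitimate question to ask, but it is not what intention-to-treat implies, and the article does not ask it consistently: MI after a third glucocorticoid cycle is left as observed. Finally, with equal SNI > 7 shares in the arms, carrying the baseline does not shift the difference. That is correct, and it is why no single bias figure can be claimed.

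**Conclusion.** The concern holds in a limited form. Three things follow from the text alone: carry-forward discards a 1-year MI that is still scheduled, contrary to the intention-to-treat claim; the value carried is not identified, and the sections conflict on whether intermediate MI values exist; and missing MI is filled by single imputation, which ignores the uncertainty of the filled value and can bias the difference either way when missingness differs by arm.

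The size is not known. Under the assumptions shown, shifts are of the order of 0.10 to 0.15 MI units against a target of 0.7, in either direction, and they vanish when the shares are equal in the two arms and, for missing MI, there is also no true effect. The stated sample size is unaffected.

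**What to change.** 1. In the primary analysis, use the observed 1-year MI, and any week 16 or 32 MI that the reconciled schedule confirms, whatever additional treatment was given. MI must therefore still be collected and kept after such treatment.
2. Handle truly missing MI by multiple imputation within arm, using baseline MI and the 16- and 32-week CAScore, Hertel and motility values, or by a likelihood-based mixed model.
3. Keep carry-forward, stating which MI is carried, and worst-case values as sensitivity analyses only.
4. Report SNI > 7 and use of a third glucocorticoid cycle by arm; the stratified Mantel-Haenszel test already planned for binary endpoints serves for this.
5. Reconcile the ultrasound schedule in Post-treatment interventions with Objective of the study, Table 5 and Statistical analysis.

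The cost is a change of wording and modest programming before database lock, with no change to sample size or recruitment. The drawback is that the estimate then includes the effect of additional treatment, so its rates by arm must be shown beside it.
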